### Power

With alpha set at 0.05, power set at 0.80, and a sample size of 34 in each group, the study is powered to enable the detection of large effect size (i.e., Cohen’s *d* = 0.80) differences in symptoms, which would be the minimum expected reduction in the RCT based on existing research [11]. Therefore, 39 individuals will be recruited in the immediate treatment group and 39 individuals in the waitlist control group, in order to hedge against attrition. Therefore, the total sample size for the study is 78.

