## Introduction

Generalized anxiety disorder (GAD) is characterized by excessive and uncontrollable worry that is accompanied by a number of physical and/or cognitive symptoms [1]. The disorder is often chronic [22] and results in considerable individual and economic burden [27, 48]. GAD can be effectively treated with cognitive behavioral therapy (CBT) [11]; however, numerous barriers to accessing treatment exist including cost, difficulty accessing a trained clinician, and geographical isolation [10, 16, 37, 40]. One way to overcome these barriers is to provide specialized treatment remotely, using digital health technologies.

Remotely delivered treatments do not require the clinician and the client to be in the same location and these interventions can be provided in either a low-intensity or high-intensity fashion [54]. Low-intensity remote treatments involve the client working through largely self-help materials either online or via a workbook, accompanied by brief asynchronous clinician contact (i.e., 10 min per week by telephone or email). High-intensity remote treatments involve using digital health technologies to provide synchronous sessions that are analogous to standard face-to-face treatment. While low-intensity remote treatments have been demonstrated to be efficacious in the treatment of GAD, with several studies demonstrating medium to large pooled effects across studies [2, 43], there is limited evidence examining high-intensity remote treatments for this condition [50]. The literature that does exist has considerable limitations (i.e., uncontrolled studies with small samples sizes) [42]. Thus, the efficacy and acceptability of high-intensity remote CBT for GAD requires further investigation.

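### The Power section's alpha, power, group size and effect size do not agree: 34 per group gives about 90% power for d = 0.80, not 80%

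*Protocol article*

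**What the plan says.** The Power section of the protocol article gives the whole calculation in a few lines. Its inputs are "With alpha set at 0.05, power set at 0.80, and a sample size of 34 in each group". With these, the study is said to be powered for "detection of large effect size (i.e., Cohen’s *d* = 0.80) differences in symptoms". To allow for attrition, "39 individuals will be recruited in the immediate treatment group and 39 individuals in the waitlist control group", which makes 78 in total.

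The section does not name a test, a one- or two-sided alpha, an attrition rate, a multiplicity adjustment or a repeated-measures correlation. Elsewhere, the Design section describes a two-group superiority trial with equal groups, and the Data storage and analysis section plans mixed linear models for the main comparison.

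**The concern.** In a two-group comparison of means with equal allocation, alpha, power, group size and standardised effect are tied together: any three fix the fourth. The Power section states all four, so it can be checked directly, and the four do not match.

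This paragraph is the article's only justification for recruiting 78 people. As written, a reader cannot tell which design target was set:

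- 80% power for d = 0.80, which needs fewer than 34 per group;
- 90% power for d = 0.80; or
- 80% power for an effect smaller than 0.80.

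The answer also determines how much loss to follow-up the trial can absorb before it falls below its target.

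**Working it through.** **Inputs (Power section, protocol article).** Alpha 0.05; power 0.80; 34 analysed per group; d = 0.80, so the SD is set to 1; equal allocation; 39 recruited per group. **Assumption:** a two-sample t-test, two-sided, because the section states neither. The one-sided case is also shown.

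**1. The plan's own figure: group size for 80% power at d = 0.80.**

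Normal approximation: n per group = 2 (z₀.₉₇₅ + z₀.₈₀)² / d² = 2 (1.960 + 0.842)² / 0.64 = 24.5, so 25.

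Noncentral t: 25.5, so 26. The check at 26 gives power 0.807, and at 25 it gives 0.791.

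The stated 34 is not reproduced. It is 8 per group above 26, or 8/26 = 31%.

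**2. Power at the stated group size.**

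Noncentrality = d √(n/2) = 0.80 × √17 = 3.30.

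- Normal approximation: Φ(3.30 − 1.96) = 0.910.
- Noncentral t with 66 degrees of freedom: 0.902.
- With all 39 per group, noncentral t: 0.937.

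**3. Solving for each input in turn, holding the others as stated (two-sided t).**

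| Quantity solved for | Stated | Recomputed |
|---|---|---|
| n per group | 34 | 26 |
| Power | 0.80 | 0.902 |
| d | 0.80 | 0.69 |
| Alpha | 0.05 | 0.017 |

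**4. Which single change makes 34 come out.** With power 0.90 and the other inputs as stated, the noncentral t gives 33.8, so 34 exactly. Alternatively, 80% power with d of about 0.69, or 80% power with alpha of about 0.017, also gives 34. None of these three is in the text.

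**5. Other readings tried.**

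- One-sided alpha 0.05: 80% power needs 20.03, so 21 per group, and 34 per group gives 94.7%. The gap widens.
- A Mann-Whitney efficiency correction (0.955 or 0.864): 25.5/0.955 = 26.7 and 25.5/0.864 = 29.5, so 27 to 30. Still short of 34.
- Attrition: it cannot explain 34, because the section adds it afterwards, going from 34 to 39.

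**6. The attrition step.** (39 − 34)/39 = 5/39 = 12.8%, and 34/(1 − 0.128) = 39. This step is consistent, but the rate is back-calculated; the section states none. If the target were 80% power at d = 0.80 under the assumed test, the tolerable loss from 39 would be 1 − 26/39 = 33%.

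**The case against.** The strongest reply is that nothing is at risk. The claim that the study is powered to detect d = 0.80 is true in the sense of at least 80%: it holds at 39 per group, at 34, and down to 26. This stands. It limits the point to a mis-stated figure, and a reader who inferred that the trial is too small for its stated effect would be wrong.

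A second reply is that the check assumes a test the article does not name, that the planned analysis is a mixed model, and that the full protocol, held with the registry, may contain the derivation. In part this stands: 26 per group and 33% tolerable loss hold only under the assumed two-sided t-test. It does not reconcile the printed figures. A one-sided test needs fewer participants, and a model that uses baseline and repeated measures would usually need fewer, not more; the article gives no correlation that would point the other way. The only Bonferroni correction mentioned is for baseline comparisons, so it does not supply the smaller alpha that 34 would require.

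A reader might also go further and set the description of d = 0.80 as an effect "which would be the minimum expected reduction in the RCT based on existing research" against the Introduction's account of remote treatment, "with several studies demonstrating medium to large pooled effects across studies", and conclude that the article contradicts itself on the expected effect. The article does not support that. The Introduction attaches those pooled effects to low-intensity treatments and says evidence on high-intensity treatment is limited. This trial tests a high-intensity treatment, and the Power section rests its effect size on a separate citation for CBT in GAD that cannot be checked here.

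**Conclusion.** The point holds as an internal inconsistency in the Power section. At two-sided alpha 0.05 with a two-sample t-test, the stated power of 0.80 should read about 0.90, or the stated effect should read 0.69, or the group size should read 26. An exact match at 90% power makes a slip in the power figure a natural explanation, but the document does not settle it.

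The direction is conservative, and neither the total of 78 nor any analysis is affected. The conclusion rests on the assumed test and sidedness; none of the alternatives tried restores agreement.

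**What to change.** The sponsor should confirm which input was used (90% power, an effect near 0.69, or an adjusted alpha) and restate the sentence so that the figures agree. If 90% power was used, suitable wording would be: *with two-sided alpha 0.05, 34 analysed per group give 90% power for d = 0.80 (equivalently 80% power for d = 0.69)*. The test should be named alongside the sidedness.

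The paragraph should also note that going from 34 to 39 per group allows for about 13% attrition (5/39), worded as what the numbers permit unless the sponsor confirms it was the planning rate.

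The restatement should not tie the calculation to a particular outcome and visit on its own authority. The Power section names neither, and the Introduction's hypothesis places the large between-group effect at 3-month follow-up, so inserting GAD-7 at post-treatment, for instance, would create a new conflict.

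Cost: a sentence or two of rewriting, with no change to recruitment, conduct or analysis.

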### Ethical approval and trial registration

The study was approved by the University of Technology Sydney Health and Medical Research Ethics Committee (UTS HREC REF NO. ETH21-5843). The trial is registered with the Australian and New Zealand Clinical Trials Registry (ACTRN12621000786897) and includes the full study protocol and participant information sheet and consent form. While not anticipated, any changes to the protocol will be updated through the ANZCTR registry.

## Discussion

GAD is a chronic and impairing mental health condition [22]. CBT is effective for GAD [11]; however, many individuals experience logistical barriers to accessing this treatment [10, 16]. High-intensity VCBT overcomes many of these barriers and may assist in the dissemination of evidence-based treatment for GAD. The primary aim of this study is to examine the acceptability and efficacy of VCBT for GAD. A secondary aim is to examine the acceptability and efficacy of a brief VCBT treatment for GAD. This will be the first study to examine the efficacy of VCBT for GAD using a controlled design. Therefore, the results of this study may inform how to best deliver VCBT for GAD. It is anticipated that the results will contribute to the growing evidence base that remotely delivered high-intensity CBT (whether standard or brief in length) is a viable option for individuals who are unable to access face-to-face treatment.

### Trial status

The protocol version number is v1.0 which was approved on 22 July 2021. Recruitment will commence in October 2021 and is expected to be completed by July 2023.

## Data Availability

De-identified data will be made available to other researchers upon reasonable request.
